**Methods:**

In this single-centered, open-labeled, randomized cohort study, patients with CKD stages G2, G3a and G3b, who visited and were treated at Tohoku University Hospital during the enrollment period were registered. We administered sodium bicarbonate or sodium-potassium citrate as the oral alkalinizing agents. A total of 150 patients with CKD will be randomly allocated into the following three groups: sodium bicarbonate, sodium-potassium citrate and standard therapy group without any alkalinizing agents. The data of performance status, venous blood test, spot urine test, venous blood-gas test, electrocardiogram, renal arterial ultrasonography and chest X-ray will be collected at 0, 6, 12 and 24 weeks (short-term study) from starting the interventions. These data will be also collected at 1 and 2 years (long-term study). The samples of plasma and serum and early-morning urine at every visit will be acquired for the analysis of renal function and surrogate uremic biomarkers.

The recruitment for this cohort study terminated in March, 2018, and the follow-up period for all the enrolled subjects will be terminated in December, 2020. The primary endpoint will be the development of originally-defined significant renal dysfunction or the occurrence of any cerebrovascular disease in the short-term study. The secondary endpoint will be the same endpoints as in the long-term study, or the patients with significant changes in the suggested the surrogate biomarkers.

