### Overview of study design

This study is a single-center, open-label, randomly-allocated cohort study, with CKD patients in stages G2, G3a and G3b. To reduce the risk of sampling error, the enrolled patients will be randomly assigned based on the stratified random sampling process by using the random sequence generated by a computer software [22, 23]. The used variables for the stratification will be age (i.e. ≥65, < 65 years old), sex, presence of diabetes mellitus, and eGFR (i.e. ≥46, < 46 ml/min/1.73m^2^). With these four variables, the enrolled patients will be divided into 16 subgroups, and then randomly allocated into the below-described three cohort groups from each of the subgroups.

The enrolled patients will be allocated into the following three cohort groups: 1) sodium bicarbonate group, 2) sodium-potassium citrate group, and 3) standard therapy group without any alkalinizing agents. Then, these three cohort groups will be measured for the targeted biomarkers in the serum and urine in the “short-term” study (i.e. at 0, 6, 12 and 24 weeks after starting the intervention) and in the “long-term” study (i.e. at 1 and 2 years after starting the interventions) to assess the effects of oral alkalinizing agents. As for the urine samples, both early-morning urine and spot urine will be collected. The above-described overview of this cohort study is shown in Fig. 1.

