### Endpoints

The primary endpoints will be **1)** the development of significant renal dysfunction, **2)** the occurrence of any kind of cerebrovascular disease between 0 and 24 weeks (short-term study) from starting the interventions. The significant renal dysfunction will be defined as the conditions that fulfill at least one of the following four criteria; 1. serum Cre level ≥ 1.5 times higher than that at 0 week, 2. eGFR decrease ≥20 ml/min/1.73m^2^ from that at 0 week, 3. proteinuria ≥3.5 g/gCr, 4. new development of urinary stones. The secondary endpoints will be the above-described criteria at 1 and 2 years (long-term study) from starting the interventions, and finding any kind of reno-protective marker associated with alkalinizing agents in both periods of study (Table 3).

**Table 3 Tab3:** Primary and Secondary Endpoints

Endpoints	Period	
Primary	Short-term	1) The development of significant renal dysfunction 1. serum Cre level ≥ 1.5 times higher than that at 0 week 2. eGFR decrease ≥20 ml/min/1.73m^2^ from that at 0 week 3. proteinuria ≥3.5 g/gCr 4. new development of urinary stones 2) The occurrence of any kind of CVD and the death
Secondary	Lon-term	1) The development of significant renal dysfunction 2) The occurrence of any kind of CVD and the death
	Short-term & Lon-term	Reno-protective marker associated with alkalinizing agents in both periods of study, for example, category II (blood tests), categoryII (urine test), urine pH and unknown surrogate biomarkers of early renal damage, including uremic toxins and known metabolites measured by metabolomics.

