### Sample size calculation

A sample size was decided based on a previous study evaluating the reno-protective effect of the sodium bicarbonate [20], in which the incidence of ESKD under treatment with and without bicarbonate were 6.5 and 33%, respectively. Based on this knowledge, we presumed the estimated incidence rate of ESKD in the sodium bicarbonate group and the sodium-potassium citrate group to be around 5 and 30%, respectively. To achieve the significant level (i.e. type-I error rate) of 5% (α = 0.05) and the statistical power of 80% (β = 0.2) with the equally allocated three groups, we estimated the ideal sample size in each group to be 50.

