### Analysis

The measured variables in the three groups will be compared by the analysis of variance (ANOVA), followed by the Bonferroni’s post-hoc comparisons. If the variables show apparent non-normal distributions, Kruskal-Wallis test will be applied as a non-parametric test. Because of the simultaneous multiple comparisons, *p*-value < 0.01 will be regarded as statistically significant. The chronological change of each variable in each group will be also evaluated. Values in each pair will be compared by the paired Student’s t-test. If the variables show apparent non-normal distributions, Wilcoxon’s rank sum test will be adopted. Comparisons of outcome with dichotomous data (i.e. frequency) between the groups will be performed by either of chi-squared test or Fisher’s exact test, based on the achieved frequency in each cell. Lastly, to clarify the correlations between urine pH, both for the early-morning urine and spot urine, and serum creatinine levels, Spearman’s correlation coefficient for each pair will be calculated, followed by the test of no correlation.

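### Event outcomes are tested without the four stratification factors: the test is valid, but conservative if allocation is balanced within strata and the factors are strongly prognostic

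*Protocol article*

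**What the plan says.** - **Allocation** (Overview of study design): "The used variables for the stratification will be age" (cut at 65 years), together with sex, diabetes and eGFR (cut at 46 ml/min/1.73m²). Then "the enrolled patients will be divided into 16 subgroups, and then randomly allocated into the below-described three cohort groups". No block size or other balancing rule is given.
- **Size** (Abstract, Methods): "A total of 150 patients with CKD will be randomly allocated into the following three groups". The Sample size calculation section gives 50 per group.
- **Primary endpoint** (Endpoints, Table 3): events between 0 and 24 weeks, the first being "the development of significant renal dysfunction". Each is a yes/no outcome per patient.
- **Test** (Analysis): "Comparisons of outcome with dichotomous data (i.e. frequency) between the groups will be performed by either of chi-squared test" or Fisher's exact test, chosen by cell frequency. No stratified or adjusted comparison is named. The section does not label a primary analysis, but this is the only test it gives for a frequency outcome.
- **Threshold** (Analysis): p < 0.01, stated in connection with multiple comparisons. The sample size uses 5%.

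**The concern.** When arms are balanced within prognostic strata, the difference between strata cannot contribute to the difference between arms. An unadjusted chi-squared or Fisher test still counts that variation as noise. Its p-values are then somewhat too large and its intervals somewhat too wide, so precision bought by the stratified randomisation goes unused. Diabetes and baseline eGFR are plausible predictors of a renal event.

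What is at stake is efficiency, not a false positive. The Discussion itself fears a negative result from too few patients, and recruitment has closed, so the choice of analysis is one of the few places left to gain precision.

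**Working it through.** **1. The plan's own figure.** With 5% v 30%, two-sided 5% and 80% power:

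n = [1.96·√(2·0.175·0.825) + 0.8416·√(0.05·0.95 + 0.30·0.70)]² / 0.25² = (1.0532 + 0.4271)² / 0.0625 = 35.1, so 36 per group (43 with continuity correction).

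The stated 50 is not reached this way. An unadjusted Fisher test at 0.05/3 has power 0.788 at n = 49 and 0.800 at n = 50, which matches 50; the article does not state that route. At n = 50, unadjusted chi-squared power is 0.92 at 5% and 0.775 at 1%.

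**2. Why balance makes the test conservative.** The unadjusted test uses variance p̄(1−p̄). Under balance within strata, the arm difference carries only the within-stratum part, p̄(1−p̄) − V, where V is the variance of risk between strata. With R = V / [p̄(1−p̄)], the true size is about 2·[1 − Φ(1.96/√(1−R))].

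Assume four evenly split factors with the same odds ratio (OR) each and a mean risk of 30%, so p̄(1−p̄) = 0.21. The number of risk factors present is 0 to 4, with weights 1, 4, 6, 4, 1 out of 16.

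- OR 3: risks 3.7, 10.4, 25.8, 51.1, 75.8%. V = 0.0388, R = 0.185, 1.96/√0.815 = 2.17, size 3.0%.
- OR 2: V = 0.0184, R = 0.088, size 4.0%.
- OR 1.5: V = 0.0069, R = 0.033, size 4.6%.

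**3. Simulation, balanced allocation.** 150 patients, 16 strata (150/16 = 9.4 each), permuted blocks of 3 (assumed), one pair of about 50 v 50, 6000 runs per scenario. Monte Carlo error for a single power near 74% is √(0.74·0.26/6000) = 0.6 points. Entries are unadjusted chi-squared / 16-stratum CMH, in %.

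| OR per factor | Size at 5% (30% v 30%) | 30% v 10%, 5% | 30% v 5%, 5% | 30% v 10%, 1% | 30% v 5%, 1% |
|---|---|---|---|---|---|
| 1 | 5.5 / 5.3 | 72.7 / 71.5 | 93.8 / 93.4 | 47.8 / 46.4 | 81.2 / 79.7 |
| 1.5 | 5.0 / 5.4 | 73.6 / 73.3 | 94.5 / 94.4 | 48.2 / 47.3 | 81.6 / 81.3 |
| 2 | 4.2 / 4.9 | 72.6 / 73.5 | 95.0 / 95.0 | 47.0 / 49.0 | 81.8 / 82.4 |
| 3 | 3.2 / 4.7 | 74.0 / 78.3 | 95.1 / 96.0 | 47.5 / 54.3 | 82.3 / 85.7 |

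Simulated sizes agree with step 2. With unequal strong factors (ORs 2, 1.3, 3, 4; assumed), 30% v 10% gives 73.1 v 76.7 at 5% and 47.4 v 51.5 at 1%, and 30% v 5% gives 95.0 v 95.5 at 5%. With moderate factors (1.5, 1.2, 2, 2.5), 30% v 10% gives 73.1 v 74.4 at 5%.

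**4. Simulation, simple randomisation within strata.** Across ORs 1 to 3, chi-squared size is 4.6-5.4%, so it is not conservative. The 16-stratum CMH test loses power: 89.2-92.7 against 93.9-94.7 for 30% v 5%, and 64.6-71.0 against 72.5-72.9 for 30% v 10%.

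**5. Main-effects adjustment.** A linear risk-difference model with the four factors and robust standard errors was also simulated. With blocking and strong factors it gains about 2 to 4 points for 30% v 10% at 5% (75.0 v 73.4 in one simulation, about 4 points in another). Under simple randomisation the change at 5% was −1.7 to +1.3 points in one simulation. The worst cost found in any setting was about 3 points, when the factors were not prognostic.

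**The case against.** **The loss is not certain.** A reader might infer that the planned p-values must be too conservative and that power must be lost. The documents do not support that. It needs balance within strata and strong factors, and the article gives neither. The stratification and the equal group sizes suggest that balance was intended, but they do not show how it was achieved. This objection stands, and the point is worded accordingly.

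**Not every gap comes from the strata.** At 20% v 3% with strong factors and blocking, the planned chi-squared/Fisher rule has 77.7% power and CMH 82.3%. A reader might put the difference down to ignored stratification. But plain chi-squared has 81.8%, so about 4 of the 4.6 points come from switching to Fisher. With factors of no prognostic value the rule still trails CMH, 77.6% v 80.3%. This objection stands: that gap is no measure of the stratification effect.

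**The textbook remedy can do harm.** CMH over 16 strata loses power without blocking. When events are few, a continuity-corrected version, used as a rough stand-in for the exact conditional test, gives 69.2% for 20% v 3%, below the planned rule. This rules out that remedy but does not touch main-effects adjustment.

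**The test is valid, and an analysis plan not shown may adjust.** The first part is conceded. On the second, the article does not merely stay silent; it names the tests. An adjusted main analysis elsewhere would depart from the published method. Still, the article is condensed, which keeps this a modest point.

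**Conclusion.** The mismatch is in the stated method: allocation is stratified by four factors, and the only test named for event outcomes ignores them. The type I error is controlled, so no false conclusion follows.

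The cost is conditional. With balanced allocation and strong factors (both assumed), true size is about 3-4% at a nominal 5%. The power given up for 30% v 10% is about 3-4 points at 5% and about 4-7 points at p < 0.01. With moderate factors, or at 30% v 5% at the 5% level, it is about 0-1 point. At 30% v 5% and p < 0.01 it reaches about 3 points only at an OR of 3 per factor. Without balance within strata the unadjusted test is not conservative.

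The 30% and 5% are the article's planning rates for end-stage kidney disease, used here only as a reference. The change is worth making because it costs almost nothing, not because the result is in danger.

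**What to change.** In the Analysis section, state that the main comparison of the event endpoints is adjusted for age group, sex, diabetes and eGFR group as main effects. Two suitable forms are a risk-difference model with robust standard errors and logistic regression, penalised if events are few. Report the adjusted effect with its 95% CI. Keep the unadjusted chi-squared or Fisher test as a sensitivity analysis. Do not make a 16-stratum or exact conditional CMH test the lead method.

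Cost: one sentence and slightly more analysis work. The factors are needed for allocation and so are known for every randomised patient; no new data or patients are required. The downside is up to about 3 points of power at the 5% level if the factors turn out not to be prognostic. The choice should be fixed before outcome data are compared by arm.

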## Discussion

Recruitment to this cohort study terminated in March, 2018, and the follow-up period for all the enrolled subjects will be terminated in December, 2020.

We will seek for new therapeutic strategies using oral alkalinizing agents for the early stage CKD patients in this CKOALA study. Based on the previous study that showed the reno-protective effects of the oral sodium bicarbonate in the animal CKD model [17], we hypothesized that administration of oral alkalinizing agents for the patients with mild and moderate stages of CKD would delay the development of ESKD. This cohort study will confirm the reported benefits of oral alkalinizing agents for suppressing CKD progression in actual human cases.

In addition to the expectation that this study will confirm the therapeutic effects of oral alkalinizing agents for CKD patients, it would also clarify the relationship between the urine pH and the chronic renal damage. Because the oral alkalinizing agents have been suggested to only alkalize the urine without changing serum pH, if the reno-protective effects of oral alkalinizing agents are confirmed, it will strongly suggest that aciduria is a definite risk factor to promote the renal damage in CKD patients.

One of the strengths of this study is that it will be conducted in a single center, which will enable us to exclude the risks of biases based on the differences between facilities and examiners. Meanwhile, there are some limitations. First, the number of enrolled subjects may remain low. If the results become negative due to inadequate sample size, we may extend the study period or plan additional randomized multi-center cohort study to achieve an adequate sample size. Another limitation is that this study will be an open-label trial. However, because the endpoints of this study are comprised of objectively measured serum and urine biomarkers that could not be affected by the preconceptions, biases based on the open-label style of this study to the given endpoints are not likely. Lastly, as for the patients’ compliance to the medications, we will interview the intake habit at all the occasions of their hospital visits.

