### Eligibility criteria for participants

The patients, 20 to 80 years of age with CKD stages G2, G3a and G3b who were treated at Tohoku University Hospital between March, 2014 and March, 2018, will be eligible for this study. As for the exclusion criteria, patients who were administered with any medications or drinks that could have possible alkalinizing effects, or patients with tolvaptan within 30 days prior to the registration will be excluded. In addition, patients with renal hypouricemia, hyperkalemia, diabetes insipidus, hypernatremia with unknown origins, morning urinary pH higher than 6.8, or serious complications of heart disease or liver disease will also be excluded. Patients with hyperuricemia, morning aciduria, or metabolic acidosis will not be excluded.

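### Long-term events are compared only as frequencies at 1 and 2 years, although the hypothesis is one of delay, patients can be censored early, and the document leaves open whether endpoints are observed after year 2

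*Protocol article*

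**What the plan says.** - **Entry.** The Eligibility criteria cover patients "treated at Tohoku University Hospital between March, 2014 and March, 2018".
- **End of follow-up.** The Discussion states that "the follow-up period for all the enrolled subjects will be terminated in December, 2020". The Abstract gives the same date.
- **Long-term endpoint.** The Endpoints section says: "The secondary endpoints will be the above-described criteria at 1 and 2 years (long-term study) from starting the interventions". The design overview also places the long-term measurements "at 1 and 2 years after starting the interventions", and the last column of Table 1 is year 2.
- **Event analysis.** The Analysis section says: "Comparisons of outcome with dichotomous data (i.e. frequency) between the groups will be performed by either of chi-squared test", with Fisher's exact test as the alternative. It names no method that uses the time of an event.
- **Early leavers.** The Censoring criteria include withdrawal of consent, moving away, high urine pH, oedema, abnormal potassium and worsening of organ symptoms. Data from patients who meet them are dropped.
- **Hypothesis.** The Discussion expects alkalinizing agents to put off the development of end-stage disease.

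**The concern.** A hypothesis of delay concerns when events occur, and a table of frequencies does not use that. A patient who leaves at 18 months without an event carries information up to 18 months. A test of proportions at 2 years must either drop that patient or count the patient as event-free. The article does not leave this choice to an unseen analysis plan, because it names the test and states the rule for leavers.

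The calendar end date adds a second question. Taken literally, it gives every patient at least 33 months of follow-up, while the endpoint stops at 24. With 50 patients per arm and few events expected, later events would matter for power. The Discussion itself fears a negative result from small numbers. Only a secondary endpoint is affected, since the primary comparison is at 24 weeks.

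**Working it through.** The plan gives no figure for long-term follow-up or power. From its sample-size section I take only 50 per arm. The stated 5% v 30% gives 36 per group at two-sided 0.05 and 80% power rather than 50, but that is a separate matter.

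**1. Calendar span (dates from the document).**
- First entrant: March 2014 to December 2020 = 81 months.
- Last entrant: March 2018 to December 2020 = 33 months.
- Last entrant's 2-year point: March 2020, which is 9 months before December 2020. Every entrant can therefore reach 24 months.

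**2. Share beyond 24 months, if patients are observed to December 2020** (assumed: uniform entry, constant hazard).
- Mean follow-up: (33 + 81)/2 = 57 months.
- Share of follow-up time beyond 24 months: 1 − 24/57 = 58% (last entrant 1 − 24/33 = 27%; first entrant 1 − 24/81 = 70%).
- Events: with h = −ln(1 − p)/24, where p is the 2-year risk, the risk to closure is F = 1 − [exp(−33h) − exp(−81h)]/(48h). The share beyond 24 months is 1 − p/F, computed before F is rounded.

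| 2-year risk p (assumed) | F | Share of events after 24 months |
|---|---|---|
| 5% | 0.114 | 56% |
| 10% | 0.220 | 55% |
| 20% | 0.406 | 51% |
| 30% | 0.562 | 47% |
| 50% | 0.791 | 37% |

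If follow-up is the scheduled 24 months, both shares are 0%.

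**3. Power by formula, no loss** (50 per arm, two arms, two-sided 0.05, assumed risks). Crude test: Φ{[√50·|p1 − p2| − 1.96·√(2p̄(1 − p̄))]/√(p1(1 − p1) + p2(1 − p2))}. Log-rank (Schoenfeld, D events): Φ(½·√D·|ln HR| − 1.96).

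| 2-year risks | HR | Crude, 24 months | Log-rank, 24 months (D) | Log-rank to December 2020 (D) |
|---|---|---|---|---|
| 10% v 20% | 0.472 | 29% | 31% (15) | 56% (31.3) |
| 10% v 30% | 0.295 | 71% | 78% (20) | 97% (39.1) |

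The Schoenfeld formula is approximate with so few events and a ratio far from 1, so I give more weight to simulation for the within-2-year contrast.

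**4. Power by simulation** (50 per arm, assumed 20% 2-year control risk).
- Yearly loss 5-10%: a 2-year log-rank test gains about 2-8 points over excluding censored patients and then testing.
- Yearly loss 0-5%, against a crude test in all randomised patients: at HR 0.5, crude 26-27% and log-rank 24-25%; at HR 0.3, 52-54% and 52-53%. There is essentially no gain.
- Yearly loss 5-10%, log-rank to December 2020 against exclude-then-test at 2 years: 39-45% against about 20-23% at HR 0.5; 76-81% against 43-47% at HR 0.3.

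**5. Crude risk under uneven loss.** With yearly event hazard h and loss hazard g, the crude 2-year proportion over all randomised patients is h/(h + g)·[1 − exp(−2(h + g))]. Assume a true 2-year risk of 20% in both arms, so h = −ln(0.80)/2 = 0.1116, and 2-year losses of 5% v 25%.
- 5% loss: g = 0.0256; 0.1116/0.1372 × (1 − 0.80 × 0.95) = 19.5%.
- 25% loss: g = 0.1438; 0.1116/0.2554 × (1 − 0.80 × 0.75) = 17.5%.

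**The case against.** The strongest reply is that the plan describes a fixed 2-year design. Every schedule in it stops at year 2, no section says that endpoints are collected later, and December 2020 comfortably covers the last entrant's 2-year point. It may simply be the administrative end of the study. A risk at a fixed horizon is a legitimate quantity to compare. In the long-term phase the laboratory criteria are scheduled only at 1 and 2 years, so exact times for them would not be known. This reply largely stands, and it rules out three stronger readings.

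- **That about half of the follow-up and events are thrown away.** A reader might infer this from the dates. The document shows no endpoint data after year 2 to discard, so the share is conditional.
- **That staggered entry biases the 2-year comparison.** It does not, because every entrant can reach 24 months.
- **That the 19.5% v 17.5% distortion applies here.** That calculation counts leavers as event-free among all randomised patients. The Censoring criteria drop leavers instead, so any distortion comes from that exclusion rule. The gap is also only 2 percentage points, or one patient in 50.

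What the reply does not answer is that frequencies after exclusion use none of a leaver's partial follow-up. Several reasons for leaving are plausibly related to treatment, so uneven departure is foreseeable. The wording on the end of follow-up also remains ambiguous beside the 2-year schedule.

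**Conclusion.** The concern holds in a limited form. The stated event analysis fits a hypothesis of delay poorly and cannot use partial follow-up, and the document does not settle whether endpoint observation stops at year 2 or runs to December 2020.

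Within the planned 2 years the power gain is modest against the stated exclusion rule and near zero against a crude test in all randomised patients. The case there rests on correct use of partial follow-up and on matching the hypothesis. The large gain in power, roughly from the low 20s to the low 40s in percent at a hazard ratio of 0.5, depends wholly on follow-up to December 2020 being obtainable.

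All event rates, hazard ratios and losses are assumed, as are uniform entry and constant hazards. Power is for two arms at two-sided 0.05. The stricter 0.01 threshold in the Analysis section would lower every power figure if it were applied to these tests. The point concerns a secondary endpoint and does not touch the 24-week primary comparison.

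**What to change.** 1. State whether endpoint follow-up ends at each patient's 2-year visit or continues to December 2020, and align the Abstract, Discussion, Endpoints section and Table 1.
2. Define the long-term event endpoint as time from randomisation to first event, censored at last contact, and keep the data that censored patients contributed. Use Kaplan-Meier curves with a log-rank or Cox comparison. For renal criteria seen only at visits, use a grouped-time model such as complementary log-log.
3. Report 1- and 2-year risks by arm from this analysis, so that the stated time points are kept.
4. Pre-state a supplementary analysis to December 2020, using records already held at the hospital.

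The cost is wording in two sections and abstraction of event dates at one centre. The supplementary analysis has a clear downside: no study visits are scheduled after year 2, so later events would come from routine care, and the document does not say whether allocated treatment continues. It should therefore stay supplementary. Censoring at last contact also assumes that leaving is unrelated to later risk. Some of the censoring criteria make that doubtful, so reasons for leaving should be reported by arm.

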## Abstract

**Background:**

Aciduria caused by urinary excretion of acidic metabolic wastes produced in daily life is known to be augmented in patients with chronic kidney disease (CKD). To evaluate the reno-protective effect of oral alkalizing agents for the improvement of metabolic acidosis and neutralization of intratubular pH in the patients with mild stages of CKD. Also, to identify reno-protective surrogate markers in the serum and urine that can closely associate the effect of urine alkalization.

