## Background

Chronic kidney disease (CKD) is a chronic progressive disease related to eating habits and lifestyle [1–3]. These days, the increment of end-stage kidney disease (ESKD) is one of the biggest problems in the management of CKD patients [4]. If the patients with CKD are not properly treated, the disease may lead to cardiovascular events as well as ESKD and renal death [5, 6]. The treatment to ameliorate tubulo-interstitial dysfunction in the progression of CKD is important for preventing the final common pathway leading to ESKD [7, 8], which is yet to be verified by clinical research.

Generally, renal dysfunction may lead to metabolic acidosis and hyperkalemia, both derived from the accumulation of acidic metabolic wastes produced in daily life [9–11]. The acidic metabolic compounds, called uremic toxins (UTs), are the substances that primarily cause the aciduria [12, 13]. The accumulation of UTs is more common in CKD patients than in healthy individuals because of the disturbed urinary excretion from the damaged kidneys [14]. Some types of UTs are known to stimulate the ROS production, which may lead to further renal tubule-interstitial dysfunction [15, 16]. Physiological acidification in renal tubules is not harmful itself; however, we previously reported that a stronger acid condition in renal tubules could result in an increased production of reactive oxidative stress (ROS), which could be aggravated by albuminuria [17]. In this previous study with a CKD animal model, an oral alkalinizing agent also improved aciduria by neutralizing renal intratubular pH and alleviating the latent metabolic acidosis.

In several past reports, treatments with some alkalinizing agents (sodium bicarbonate and sodium citrate) ameliorated renal damage in CKD patients with eGFR < 60 ml/min/1.73m^2^ [18–20]. In addition, intake of fruits and vegetables also ameliorated the renal dysfunction and high blood pressure [21]. Oral alkalinizing agents are also suggested to be useful for prolonging the initiation of hemodialysis by some unknown mechanisms, but this possible effect is still to be scientifically established.

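### A benefit of alkali would show an effect of alkali therapy; it cannot by itself be credited to the correction of aciduria, as the Discussion plans to do

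*Protocol article*

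**What the plan says.** The Aims section of the protocol article describes renal protection obtained by neutralizing aciduria. The Discussion then says how a positive result will be read: "if the reno-protective effects of oral alkalinizing agents are confirmed, it will strongly suggest that aciduria is a definite risk factor". The reason given in the same sentence is "Because the oral alkalinizing agents have been suggested to only alkalize the urine without changing serum pH".

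Elsewhere the article describes the treatment as acting on two things:

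- **Abstract, Background.** The purpose is to evaluate the agents "for the improvement of metabolic acidosis and neutralization of intratubular pH".
- **Background.** In the earlier animal study, "an oral alkalinizing agent also improved aciduria by neutralizing renal intratubular pH and alleviating the latent metabolic acidosis".
- **Eligibility criteria.** "Patients with hyperuricemia, morning aciduria, or metabolic acidosis will not be excluded". On the urine side, the only pH limit is the exclusion of "morning urinary pH higher than 6.8".

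The Overview of study design sets two alkali arms (sodium bicarbonate, sodium-potassium citrate) against standard therapy without alkali. Under Drug intervention, dose is adjusted to early-morning urine pH. Under Analysis, measured variables are compared between the three groups by ANOVA or Kruskal-Wallis, and urine pH is related to serum creatinine by Spearman's coefficient. Serum HCO3- is in blood Category I (Table 2), which Table 1 schedules at all six time points.

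**The concern.** The Discussion makes the aciduria conclusion depend on one thing only: that alkali is shown to protect the kidney. That step is valid only if alkali has no other route to the kidney. The article itself names another route, relief of metabolic acidosis, and admits the patients in whom that route is most plausible.

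What is at stake is the mechanistic claim, which the stated aim puts at the centre of the study. A real benefit of alkali could come partly or wholly from systemic acid-base correction. The plan, followed exactly, would still report it as strong support for aciduria as a cause of renal damage.

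**Working it through.** The point is about inference. The article gives no figure on it to reproduce, so the check sets the passages side by side.

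**Step 1. The premise against the rest of the article.**

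| Place | Urine or tubular pH | Systemic acid-base status |
|---|---|---|
| Discussion | alkalized | serum pH suggested to be unchanged |
| Abstract, Background (purpose) | neutralized | metabolic acidosis to be improved |
| Background (animal model) | neutralized | latent metabolic acidosis relieved |
| Eligibility criteria | morning pH above 6.8 excluded | metabolic acidosis admitted |

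The Discussion's restriction to urine alone does not fit the second and third rows. The fourth row means that the trial may include patients in whom the systemic route is open. Unchanged serum pH would not close that route either: the acidosis in the animal study is called latent, and latent acidosis could be relieved without a visible change in pH.

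**Step 2. What randomization identifies.** Write the total effect of assignment to alkali on the renal outcome as

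T = U + S

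where U is the part through urine pH and S the part through systemic acid-base status. The comparison between arms estimates T. It is one estimate for two unknowns. Reading T as U requires S = 0, which is the premise that Step 1 puts in doubt. Both active arms give systemic alkali and the control gives none, so no contrast between arms isolates U.

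**Step 3. Whether the Spearman correlation helps.** It does not separate U from S, for two reasons. Urine pH after randomization is changed by treatment, so its correlation with creatinine is not a randomized comparison. In the alkali arms, dose is also adjusted to early-morning urine pH, so a patient's urine pH and alkali dose are tied together. As described, the correlation is unadjusted.

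**Step 4. Size, under assumptions only.** Let s be the share of patients with metabolic acidosis, and suppose that benefit occurs only in them, through S, with risk reduction d. The trial would then observe T = s × d, with U = 0. The article does not give s; take 10% to 40%. For d, borrow the planning gap in the Sample size calculation, 30 − 5 = 25 percentage points. Those are assumed ESKD rates, not rates of the primary composite.

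- s = 10%: 0.10 × 25 = 2.5 points
- s = 40%: 0.40 × 25 = 10 points

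In this scenario the whole of T would be credited to aciduria and none of it would belong there. The figures illustrate the logic; they do not estimate anything in this trial.

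**The case against.** The case on the other side has real weight.

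- **It is a hedged Discussion sentence.** It is conditional on a confirmed benefit and speaks of strong suggestion, not proof. No endpoint, sample size or test depends on it. This stands, and a reader should not infer that the article claims proof. The sentence is nevertheless an inference rule stated in advance, it matches the stated aim, and it turns on benefit alone.
- **The conflict is not a refutation.** The abstract states a purpose, and the Background reports an animal model without reporting a change in serum pH. This also stands. A reader might infer that the article disproves its own premise; it does not. But the premise is itself only something that has been suggested, so it cannot carry the conclusion untested.
- **Serum data will be compared anyway.** The ANOVA of measured variables covers HCO3-, so it would be wrong to say that the plan ignores systemic acid-base status. What remains is that the Discussion's conclusion does not depend on that result.
- **Subgroup or mediation analyses may be in a document not shown.** Correct, and their absence from an article is no finding. The finding is the inference that the article does state.
- **Acidosis is not a stratification factor.** This is no defect here. Stratifying would improve balance but could not separate two pathways moved by the same drug.
- **The illustrated effects would rarely be confirmed.** With 50 per arm and an assumed control risk of 30%, a true reduction of 2.5 to 10 points gives one alkali arm a significant benefit with probability of about 5% to 21% at p < 0.05, and 1% to 8% at the article's p < 0.01. This stands, and it is a further reason not to lean on the illustration. It does not make the inference valid when a benefit is found.

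**Conclusion.** The concern holds for the conclusion drawn, not for the trial's comparison. Alkali versus no alkali identifies the effect of alkali therapy. Crediting that effect to aciduria needs the further assumption that nothing runs through systemic acid-base status, and the article's own purpose, animal evidence and eligibility criteria conflict with that assumption. The planned correlation does not supply what is missing.

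A stronger reading would be that the design is unsound or the arm comparison biased. The documents do not support it: the randomized estimate of alkali's effect is untouched by this point. Nor do they show that alkali will change serum acid-base status in these patients.

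No numerical size can be given from the documents. The 2.5 to 10 points above rest wholly on an assumed share with acidosis, an assumed risk reduction and no benefit in other patients. The verdict itself needs none of those figures. The change should be made, because it alters what the trial may conclude and costs little.

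**What to change.** 1. **Limit the Discussion's conclusion.** State that a confirmed benefit would show an effect of oral alkali therapy, and describe the aciduria mechanism as a hypothesis only. Remove or qualify the premise that only the urine is affected, so that it agrees with the abstract and Background.
2. **Add exploratory support from data already collected.** Report the difference between arms in the change in serum HCO3-, with confidence intervals. Report the interaction of treatment with baseline HCO3- as a continuous variable, with the estimated treatment effect at normal baseline HCO3- and its interval. Define the normal value in advance.
3. **Do not read a non-significant HCO3- difference as equality.** With about 50 patients per arm, and fewer without acidosis, such a result could not establish that systemic status was unchanged. It must not license the aciduria claim.

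The cost is confined to wording and analysis, since serum HCO3- is scheduled at all six visits and no new data are needed. The price is a weaker permitted claim and an exploratory estimate that will be imprecise.
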